**Methods and analysis:**

A total of 72 breast cancer participants scheduled for axillary lymph node dissection will be recruited from Yunnan Provincial Hospital of Traditional Chinese Medicine and the First Affiliated Hospital of Kunming Medical University. They will randomly assigned in a 1:1 ratio to the TEAS group or the Sham TEAS group, with 36 cases in each group. Treatment will be administered once daily from the first day before surgery to the third day after surgery (paused on the surgery day), and subsequently twice a week for 4 consecutive weeks, totaling 12 intervention sessions. This will be followed by an 18-month follow-up period. The primary outcome measures are the incidence and time of onset of lymphedema within 18-month postoperatively. Secondary outcome measures include: VAS scores for perceived swelling and lymphedema-related symptoms evaluated at baseline (T0), from preoperative to postoperative day 3 (T1-T4), upon completion of twice-weekly post-discharge treatments (T5-T12), and during monthly follow-ups until 18 months postoperatively (T13-T29); changes in circumference, edema stage, and severity of the affected limb evaluated at T0, before and after treatments from preoperative to postoperative day 3 (T1a/b-T4a/b), before and after twice-weekly post-discharge treatments (T5a/b-T12a/b), and at T29; skin thickness ultrasound and lymphangiography of the affected limb performed at T0, T2, T12, and T29; and serum inflammatory factor levels measured at T0, T4, and T12. Adverse events occurring during the trial will be recorded.

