## Methods and analysis

### Study design

This study is a multicenter, prospective, randomized, sham-controlled, parallel-group clinical trial designed to evaluate the efficacy and safety of TEAS pretreatment for lymphedema in patients undergoing ALND for breast cancer. A total of 72 eligible participants will be recruited and randomly assigned in a 1:1 ratio to either the TEAS group or the Sham TEAS group. The study protocol adheres to the Consolidated Standards of Reporting Trials (CONSORT) 2025 statement and the Standards for Reporting Interventions in Clinical Trials of Acupuncture (STRICTA) guidelines. The trial flow is illustrated in **Figure 1**, and the schedule for participant recruitment, interventions, and assessments is presented in **Figure 2**.

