### Randomization and blinding

Eligible patients will be randomly assigned in a 1:1 ratio to receive either TEAS or Sham TEAS treatment. An independent staff member will assist in establishing and managing the randomization database. Patients in both the TEAS and Sham TEAS groups will be blinded to their group allocation. During each session, they will receive treatment in a closed unit. Except for the acupuncturists, all other researchers, including statisticians, outcome assessors, and data analysts, will be blinded to the group allocation. Furthermore, the acupuncturists will not be involved in outcome assessment or data analysis.

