### Data analysis

Software and Data Handling: All statistical analyses will be performed by an independent statistician using SPSS 25.0 software (IBM, Armonk, NY). Missing data will be imputed using the Last Observation Carried Forward (LOCF) method.

Normality and Continuous Variables: Measurement data will be assessed for normality using the Shapiro-Wilk (S-K) test. Data conforming to a normal distribution will be expressed as mean ± standard deviation (SD). Intra-group comparisons (pre- and post-treatment) will be analyzed using the paired samples t-test, while inter-group comparisons will be performed using the independent samples t-test. Measurement data that does not follow a normal distribution will be analyzed using non-parametric rank-sum tests.

Categorical Variables and Significance: Enumeration data (categorical data) will be presented as percentages or constituent ratios, and differences between groups will be analyzed using the Chi-square (χ²) test. All statistical tests will be two-sided, with the significance level set at αt 0.05. A P-value < 0.05 will be considered statistically significant.

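### The named between-group tests pool two hospitals with no hospital term; stratifying or adjusting by hospital is a cheap gain of modest size, not the repair of an invalid test

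*Protocol article*

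**What the plan says.** Study design in the protocol article states: "This study is a multicenter, prospective, randomized, sham-controlled, parallel-group clinical trial". The abstract says that participants "will be recruited from Yunnan Provincial Hospital of Traditional Chinese Medicine and the First Affiliated Hospital of Kunming Medical University", so there are two centres.

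On allocation, Randomization and blinding says: "Eligible patients will be randomly assigned in a 1:1 ratio to receive either TEAS or Sham TEAS treatment". It adds: "An independent staff member will assist in establishing and managing the randomization database". It neither states nor rules out stratification or blocking by hospital.

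On analysis, the Data analysis section commits to specific tests:
- Categorical outcomes, which include the incidence of lymphedema: "differences between groups will be analyzed using the Chi-square" test.
- Normally distributed measurements: "inter-group comparisons will be performed using the independent samples t-test".
- Other measurements: "Measurement data that does not follow a normal distribution will be analyzed using non-parametric rank-sum tests".
- Sidedness: "All statistical tests will be two-sided, with the significance level set at" 0.05.

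No test has a hospital term or stratum, and no adjusted or stratified analysis is named. The limitations in the Discussion list tumour, surgical and treatment factors as possible confounders, but not hospital.

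**The concern.** One centre is a traditional-medicine hospital and the other a university hospital. Case mix, surgical practice, delivery of the background preventive care, and the people who handle the tape and the ultrasound probe may differ between them. The protocol itself treats operator variation as real: its measurement instructions ask for one tape and, if possible, one measurer. That is hard to achieve across two sites.

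A pooled test treats all 72 patients as one sample. Two things can follow:
- If allocation ignores hospital, the arms can by chance contain different shares of each hospital, and the pooled estimate carries that difference.
- Whether or not allocation uses hospital, hospital-to-hospital variation stays in the error term. If allocation is balanced within hospital, the pooled standard error is too large for the design.

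With 36 patients per arm, avoidable noise deserves attention, and the remedy costs little.

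**Working it through.** **Inputs from the protocol article.** Two hospitals (abstract; Recruitment and informed consent). 30 per group with a 20% allowance for dropout (Sample size calculation). An incidence of about one-quarter (Discussion). The planned total reproduces: 30 × 2 × 1.20 = 72, or 36 per arm. The proposed change does not alter it.

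**Assumptions, because the document gives no figures by hospital.** Hospitals recruit 36 each. Control-arm incidences in the two hospitals range from 0.25/0.25 to 0.30/0.80. For continuous outcomes the hospitals differ by 0.5 to 1.0 within-hospital SD.

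**Step 1: chance imbalance if allocation is unstratified.** The number of one hospital's patients in the TEAS arm is hypergeometric (72 patients, 36 from that hospital, 36 drawn), with mean 18.
- P(split 21:15 or worse) = 0.238.
- P(split 22:14 or worse) = 0.098.

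At 22:14 the hospital share differs between arms by (22 − 14)/36 = 0.222. A hospital incidence difference of 10 to 20 points then shifts the treatment difference by 0.222 × 10 = 2.2 to 0.222 × 20 = 4.4 points.

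For scale, take 25% v 12.5% (a halving of the one-quarter figure) with 36 per arm. The standard error of the difference is √(0.25 × 0.75/36 + 0.125 × 0.875/36) = 0.091, or 9.1 points. The shift is therefore about a quarter to a half of one standard error.

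**Step 2: incidence, pooled chi-square v Cochran-Mantel-Haenszel (CMH).** Simulation with N = 72, 20,000 runs per setting, a 50:50 hospital split and, for power, a within-hospital odds ratio of 0.25. Power is for unstratified allocation.

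| Control rates | Difference (points) | Power, chi-square | Power, CMH | Type I error of chi-square, unstratified | Type I error of chi-square, within hospital |
|---|---|---|---|---|---|
| 0.25/0.25 | 0 | 0.536 | 0.523 | 0.049 | 0.053 |
| 0.20/0.30 | 10 | 0.531 | 0.519 | 0.049 | 0.048 |
| 0.15/0.35 | 20 | 0.510 | 0.511 | 0.051 | 0.043 |
| 0.40/0.75 | 35 | 0.695 | 0.749 | 0.048 | 0.035 |
| 0.30/0.80 | 50 | 0.576 | 0.691 | 0.046 | 0.021 |

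Up to a 20-point difference the two tests agree within about 1.3 points, slightly in favour of the pooled test when the hospitals are alike. CMH gains 0.749 − 0.695 = 5.4 points at 35 and 0.691 − 0.576 = 11.5 points at 50. Type I error of CMH stays between 0.049 and 0.054 throughout.

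**Step 3: continuous outcomes.** With equal hospitals, a difference of D within-hospital SD raises the total variance from 1 to 1 + 0.25D².
- D = 0.5: variance 1.0625, equivalent to losing 1 − 1/1.0625 = 5.9% of the sample.
- D = 1.0: variance 1.25, equivalent to losing 1 − 1/1.25 = 20%.

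Take 36 per arm and an assumed effect of 0.67 within-hospital SD, which gives the adjusted analysis power of about 0.80. The unadjusted t-test then has a standardised effect of 0.67/√1.0625 = 0.650 (power 0.78) or 0.67/√1.25 = 0.599 (power 0.71). The loss is about 2 to 9 points.

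**The case against.** The strongest reply has four parts.

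**Allocation.** A 1:1 ratio is as true of hospital-stratified blocks as of simple randomization, and a condensed article commonly leaves strata to the full protocol. This stands. Silence on strata is not treated here as a fault; the point rests on the tests that Data analysis names.

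**Validity.** An unadjusted comparison of randomized arms is valid. This stands too. A reader might infer that pooling biases the result, or that the pooled tests are weaker whatever the circumstances. Neither is supported. Over randomizations the chi-square holds its type I error (0.046 to 0.051 when allocation is unstratified), and at hospital differences of 0 to 20 points it matches CMH or is marginally better. The 2.2 to 4.4 point shift is chance imbalance, which the unadjusted standard error already covers.

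**Existing controls.** Unified training, standard operating procedures, common basic treatment and repeated tape readings reduce hospital variation. A stable hospital level cancels in the paired within-group tests, in before-and-after differences and in affected-versus-healthy limb comparisons. So the point applies to between-group tests, and less to those based on such differences. It remains for incidence and for outcomes compared as levels, because training does not equalise case mix or surgery.

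**Basis for the size.** The document supports no particular hospital difference. That is correct, and is why ranges are shown. The change is justified by the small cost of stratifying set against a possible, not demonstrated, gain.

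**Conclusion.** The concern holds in a limited form. The trial has two hospitals, and the between-group tests named in Data analysis ignore them. With unstratified allocation, this leaves chance imbalance uncorrected and hospital variance in the error term. With allocation within hospital, it makes the pooled tests conservative: the chi-square's type I error is 0.043 at a 20-point hospital difference and 0.021 at 50 points.

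For incidence the practical gain is negligible unless hospital rates differ by much more than 20 points. For continuous outcomes it is about 2 to 9 points of power at hospital differences of 0.5 to 1.0 SD. All these figures depend on assumed hospital differences, equal recruitment and the assumed treatment effects. This is a modest improvement worth making, and it does not invalidate the stated tests.

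**What to change.** Before unblinding, state in Data analysis that between-group comparisons are stratified or adjusted by hospital:
- **Incidence:** a Cochran-Mantel-Haenszel test with a weighted risk difference.
- **Time of onset:** a hospital-stratified method, such as a stratified log-rank test or Cox model. This is part of the primary outcome, so it should not be left out.
- **Continuous outcomes:** hospital as a fixed factor.
- **Rank-based comparisons:** a hospital-stratified rank test.

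Also state in Randomization and blinding whether allocation is within hospital. If it is not, use separate lists per hospital for participants still to be randomised. Trial status reports 10 enrolled by July 2025, leaving 72 − 10 = 62 at that date. Recruitment was planned to end in January 2026, so this part may come too late. The analysis change remains possible as long as it is fixed before unblinding; adding it afterwards would look data-driven.

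The cost is a few sentences, one degree of freedom in the continuous models, and up to about 1.5 points of power if the hospitals turn out alike. The sample size stays at 72.

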### Data collection and management

All data will be initially recorded in Case Report Forms (CRFs) and subsequently entered into the study’s data management system by the researchers. Relevant patient characteristics, such as names, ID numbers, and telephone numbers, will be recorded in an anonymized format. For participants who discontinue treatment or deviate from the protocol, researchers will make every effort to supplement missing outcome data during the follow-up phase. The database will be locked after the last participant has completed the final follow-up and the data has been verified by two personnel; once locked, no modifications can be made. All participant files will be encrypted, stored, and centrally managed by the research center with strict confidentiality to ensure data security and traceability.

### Quality control

The design of this trial has been evaluated and refined by experts in acupuncture, breast surgery, statistics, and methodology. Any modifications to the trial protocol will be reported to the ethics committee, and any changes to the database will be recorded in the Case Report Forms (CRFs). Furthermore, to ensure trial quality, all researchers, including acupuncturists, data collectors, and statisticians, will undergo unified training. Licensed acupuncturists possessing a master’s degree in medicine and clinical experience are required to strictly adhere to standardized intervention procedures. All physicians must complete a one-day professional training session to familiarize themselves with the treatment protocols. To ensure consistency across participants, a set of clinical Standard Operating Procedures (SOPs) will be formulated. The aforementioned measures are intended to ensure the feasibility and safety of the clinical study.

### Trial status

This trial is currently in the recruitment phase. As of July 2025, 10 participants have been enrolled.

### Patient and public involvement

Patients and/or the public were not involved in the design, conduct, reporting, or dissemination plans of this research.


According to TCM theory, BCRL is not directly caused by the cancer itself but by damage to local lymphatic vessels and meridians during ALND. The Lung Meridian of Hand-Taiyin “emerges transversely from the lung system to the axilla,” the Heart Meridian of Hand-Shaoyin “emerges from the axilla,” and the Pericardium Meridian of Hand-Jueyin “descends to the axilla,” indicating that the axilla is the convergence point of the Three Yin Meridians of Hand. ALND primarily damages these meridians, leading to obstructed Qi flow in the axilla and upper limb. In this study, selected acupoints include Tianfu (LU3) and Taiyuan (LU9) of the Lung Meridian, Qingling (HT2), Shaohai (HT3), and Xinshu (BL15) of the Heart Meridian, and Geshu (BL17), which is the Influential Point of Blood, capable of resolving stasis and unblocking collaterals. The combination of these acupoints aims to improve lymphatic drainage and enhance local blood circulation.

The primary objective of this study is to determine the efficacy of TEAS for BCRL. In addition to recording subjective indices (e.g., VAS scores for perceived swelling and lymphedema-related symptoms) and objective clinical parameters (e.g., limb circumference changes and edema staging), this study highlights the crucial role of lymphatic system visualization and morphological monitoring in early diagnosis and assessment. Given that the initial pathological changes in lymphedema often manifest as slight thickening of the skin rather than an increase in subcutaneous tissue volume, this study incorporates ultrasound monitoring of skin thickness to provide early morphological evidence that is more sensitive than circumference measurements (23). Furthermore, to objectively assess the immediate impact of surgery on the lymphatic system, this study emphasizes the importance of preoperative baseline (T0) assessment. Serial near-infrared (NIR) fluorescence imaging, performed pre- and post-operatively (24), enables the dynamic observation of functional lymphatic vessel damage and the subsequent formation of collateral circulation. NIR possesses excellent tissue penetration, sensitivity, and high resolution, enabling non-invasive real-time tissue imaging. Indocyanine green (ICG) is a common NIR fluorescent dye used in BCRL assessment. Upon subcutaneous injection, ICG binds to plasma proteins in lymph, emitting detectable fluorescent signals that are transduced into lymphatic system images (25). The advantages of fluorescence imaging include the absence of ionizing radiation, minimal trauma, repeatability, real-time imaging, and ease of operation, making it suitable for preoperative assessment, intraoperative tracing, and postoperative follow-up. Furthermore, to comprehensively evaluate the intervention, this study will investigate the impact of TEAS on serum inflammatory factor levels. Finally, we will evaluate the statistical differences between TEAS and sham TEAS regarding BCRL incidence and quality of life.

This study has several limitations. Firstly, BCRL occurrence is closely related to tumor site, invasion extent, surgical method, and history of radiotherapy or chemotherapy; these confounding factors may influence result interpretation. Therefore, identifying independent risk factors for BCRL is crucial. Secondly, BCRL is not inevitable, and its onset varies from immediately post-surgery to months or years later; thus, universal preventive intervention for all patients may increase health economic costs. Furthermore, patient treatment compliance poses a challenge. Finally, regarding the placebo control design, although maintaining the minimum sensation threshold for 30 seconds helps achieve blinding, it may underestimate the short-term effects of TEAS. Conversely, reducing the current intensity increases the risk of unblinding. Future research should further optimize trial design, explore the combined efficacy of TEAS with other therapies, and evaluate its generalizability and long-term effects in diverse populations.
